### Secondary outcomes

Secondary outcomes are the change in BC, FF, bone mineral density (BMD), inflammatory cytokines, PA, and sedentary behaviors.

#### BC and BMD

The BC assessment will be performed according to the protocol described by Park et al. (40), using the Inbody 770 Body Composition Analyzer (CA, United States), which measures and analyses body mass index, body fat mass, body fat percentage, fat-free body mass, fat-free mass percentage, and visceral fat level (41). BMD of the heel bone in older people will be measured using a KJ 3000S+ ultrasound bone densitometer. The T-value is used to express the standard deviation of the participants’ BMD compared with the mean value of the same-sex peers. BMD is one of the most important methods for diagnosing osteoporosis, T ≤ −2.5SD indicates osteoporosis, T ≥ −1.0SD indicates normal bone mineral density, and −2.5SD < T < −1.0SD is considered bone loss (42, 43).

##### Functional performance assessment

Functional performance evaluates muscular strength (lower and upper body), aerobic capacity, flexibility, and balance.

###### Muscular strength

(1) 30-s chair rise test: this is a simple but reliable measure of lower extremity strength. It measures the number of times a participant can complete a rise and sit in 30 s without holding the chair (44, 45). (2) 30-s arm curl test: upper extremity strength is tested using the 30-s arm curl test. It measures the number of times the participant completes flexion-extension of the elbow in 30 s (46). (3) HGS: this is a fundamental indicator for determining frailty and disability. The left and right handgrip strength is measured alternately using the Jamar® Hydraulic Hand Dynamo meter (United States), three times each, and the maximum left/right HGS measurement is recorded (47, 48).

###### Flexibility

(1) Chair sit and reach test: the participant is seated on the edge of a chair without armrests, with the tested leg straight ahead at the knee, heel touching the ground, and dorsiflexion of the foot at a 90° angle, and the other leg naturally bent flat on the ground. The overlapping middle fingers of both hands are aligned as far as possible toward the toes. The distance between the tip of the middle finger and the tip of the foot is measured (49, 50). (2) Back scratch test: the participant stands upright with the dominant upper limb flexed at the shoulder and elbow, fingertips down, and palm inward to touch the center of the back. The other hand goes around the waist palm outward, fingertips upward with the back of the hand to touch the center of the back, and the hands are folded or touched as much as possible (51, 52).

###### Balance

(1) Timed up-and-go (TUG) test: it is useful for identifying older adults who may benefit from exercise interventions to reduce the risk of falls. The participant sits in a standard 45 cm highchair, gets up from the chair and then walks forward as quickly as possible for 3 m, and then returns to a sitting position; the time taken to complete the task is recorded, <10s is considered as normal (53). (2) Single-leg stance test: it is a significant predictor of injurious falls. Participants are instructed to balance on one leg without upper body support and the longest time standing on one leg is recorded (54).

###### Aerobic endurance

(1) 4-m gait speed test: the participant is instructed to walk a straight-line distance of 4 m on a flat surface at normal speed and the time taken to walk is recorded. Repeated measurement 2 time and the shortest time will be taken as the result of the test, a gait speed of <0.8 m/s was found to have good sensitivity and specificity for identifying frailty in old age (55, 56). (2) 2-min standing marching test: the participant is instructed to march in place, raise one knee above the height of the other knee, and count the number of times the right knee is raised (above the other knee) in 2 min (57, 58).

#### PA and sedentary behaviors

The PA characteristics will be measured using the ActiGraph wGT3X-BT activity monitor (ActiGraph, United States), which has been validated to measure PA intensity or activity energy expenditure in adults. The sampling frequency of ActiGraph wGT3X-BT will be set to 100 Hz, and participants will be instructed to wear the device 24 h a day for at least 7 days. Moderate-to-vigorous intensity PA levels [>3 metabolic equivalents of task (MET)] will be calculated using the Freedson cutoff point of ≥1952 counts/min (CPM), using the vertical axis (VA) in minutes/day. Sedentary behavior (<1.5 MET) will be calculated using a Freedson cutoff point of <100 CPM, using the VA in minutes/day, and the data will be processed using the ActiLife 6 software system (59). The wearable device automatically transmits to the healthcare professionals’ platform in real-time during the data collection process, thus validating its accuracy.

#### Inflammatory biomarkers

A registered nurse will collect approximately 5 mL of whole blood from the participants’ anterior elbow vein in the morning (after 12 h of fasting) into polypropylene tubes containing ethylenediaminetetraacetic acid (EDTA) and centrifuge the tubes at 4,000 rpm for 10 min at 4°C. All tubes will be collected, processed, and stored at −80°C in a refrigerator. Simultaneous measurement of 48 different inflammatory markers in plasma samples by Luminex assay according to previous literature (6), including serum levels of chemokines (CXCL8/IL-8, CCL5/RANTES, CXCL9/MIG, CCL2/MCP-1, CCL11/Eotaxin and CXCL10/IP-10, CCL4/MIP-1β, CCL7/MCP-3, CXCL1/GROα, CCL3/MIP-1α, CCL28/CTACK, and CXCL11/SDF-α) and cytokines (IL-2, IL-3, IL-4, IL-5, IL-6, IL-7, IL-9, IL-10, IL-12, IL-13, IL-15, IL-16, IL-17A, IL-18, IL-1β, TNF-a, TNF-β, IFNγ, and IFNα). Samples will be measured in duplicate.

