**Methods:**

This is an open-label, prospective, two-arm parallel randomized controlled trial with allocation concealment and outcome assessment blinding. We aim to recruit 140 pre-frail community-dwelling older adults who will be randomized into two groups. The control group will receive a health education program, while the intervention group will receive *PF-Life* training as planned for 1 year. The proportion of pre-frailty, functional performance (muscular strength, aerobic capacity, flexibility, and balance), body composition, and physical activity will be measured at pre-intervention, post-intervention, and 12-month follow-up. Inflammatory biomarkers will also be collected to explore the underlying mechanisms.

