Therefore, exploring how technological innovation can support such an exercise program is imperative. Recent advances in digital technology, such as wearable sensors and smartphone applications, provide an opportunity to improve uptake and sustainability of exercise programs (25). For instance, objective physical activity (PA) monitoring using wearable sensors can be useful in developing motivational strategies to enhance daily activity (26). Particularly, mobile health (mHealth) platforms consisting of apps and web portals synchronized with wearable devices appear to be an effective way to enable self-management and remote monitoring of home-based exercise (27, 28). To date, little is known about the potential application of mHealth platforms to lifestyle-integrated multicomponent exercise and their effectiveness to prevent pre-frailty.

We have developed a lifestyle-integrated multicomponent exercise program, namely *PF-Life*, based on the mHealth platform in line with current evidence-based principles. This program offers tailored, progressive, lifestyle-integrated multicomponent exercises that incorporate behavioral change strategies such as timely motivation, feedback, reminders, and monitoring. The current randomized controlled trial (RCT) aims to evaluate the effectiveness and the underlying mechanisms of the *PF-Life* program to reverse pre-frailty in community-dwelling older adults. We hypothesize that *PF-Life* reverses pre-frailty, enhances functional fitness (FF), including endurance, flexibility, muscular strength, and balance, improves body composition (BC), increases daily PA, and modulates levels of inflammatory cytokines in a Chinese pre-frail population throughout a 12-month outcome assessment.

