## Methods

### Study design and setting

This is an open-label, prospective, two-arm parallel RCT with balanced randomization (1:1), allocation concealment, and outcome assessment blinding. The study protocol employs the Standard Protocol Items: Recommendations for Interventional Trials (SPIRIT) guideline and the Consolidated Standards of Reporting Trials (CONSORT) statement for clinical trial transparency (29). The trial will be conducted at the Fujian Geriatrics Center, which is the largest geriatrics specialty among general hospitals in Fujian Province, China. Participants will be recruited from the *Fujian Prospective Aging Cohort* according to the screening criteria and randomly allocated to two groups: the *PF-Life* program (intervention) group and the health education (control) group. Data from each participant group will be collected at four different times: screening assessment, post-randomization baseline assessment, 4-month outcome assessment, and 12-month outcome assessment. The flowchart of the study protocol is displayed in Figure 1.

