#### Exercise program

The exercise program is based on and expands upon the standardized LiFE program (21, 38). It is a multi-component exercise program that incorporates four basic functional areas: aerobic conditioning, muscle strengthening, flexibility, and balance training. When designing content, each exercise was specifically chosen to be relevant to daily living activities in the home environment and was easy to incorporate or mimic daily life, such as lifting the toes and heels, chair rise, back scratch, simulated towel wringing, farmer’s walk, etc.

There are 16 sets in the three levels of difficulty based on functional performance: elementary, intermediate, and advanced with increasing complexity. Personalized exercise programs are customized based on the assessment of the participant’s current level of FF in endurance, balance, flexibility, and strength. The exercise programs follow the principle of progression, increasing the exercise load by adding more repetitions and longer training times and using ankle weights at higher levels. For example, the first month of strength training begins with 3 reps per set for 3 sets at 30% one repetition maximum (1RM) loading and progresses in the second month with a gradual progression to 5 reps per set for 3 sets at 80% 1RM. Frequency, Intensity, Timing, and Type (FITT) are based on the FITT Guidelines for Older Adults (39). Participants are advised to train five times a week at their preferred time for 16 weeks. After 16 weeks, participants may continue to use the program for as long as they choose. In addition to the multicomponent exercises, participants are encouraged to increase daily PA and decrease sedentary time through visual charts showing daily PA progress. The exercise program was developed by the research team in consultation with experts in geriatrics, sports medicine, and rehabilitation medicine. The instructional videos were filmed in advance and embedded in the mHealth platform.

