### Waitlist control group

The control group will maintain their regular lifestyle and daily routine activities. They will also receive four health education sessions once a month, delivered by geriatric specialist nurses in person or via WeChat, including the benefits of exercise for frailty. If the intervention proves effective for the intervention group, the control group will be invited to participate at the end of the study.

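### The cytokine draw is timed to the clock and to fasting but not to the last exercise session, so at 16 weeks any short-term after-effect could not be separated from the training effect

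*Protocol article*

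**What the plan says.** Under Inflammatory biomarkers, the article specifies the draw in detail: from the "anterior elbow vein in the morning (after 12 h of fasting", with tube type, centrifugation, storage temperature and duplicate assay also stated. Time since the last exercise session is not among the conditions, and no other section ties it to the draw.

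Under Exercise program, the intervention arm's schedule is: "Participants are advised to train five times a week at their preferred time for 16 weeks". The worked example of strength training reaches "a gradual progression to 5 reps per set for 3 sets at 80% 1RM" in the second month. Later use is optional: "After 16 weeks, participants may continue to use the program for as long as they choose".

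Under Waitlist control group: "The control group will maintain their regular lifestyle and daily routine activities".

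Study design and setting names a "4-month outcome assessment, and 12-month outcome assessment", and Table 1 places the cytokines at baseline, 16 weeks and 1 year. On purpose, the abstract says "Inflammatory biomarkers will also be collected to explore the underlying mechanisms", and the Background hypothesis is that the program "modulates levels of inflammatory cytokines in a Chinese pre-frail population throughout a 12-month outcome assessment".

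**The concern.** The sampling rule holds constant two things that randomisation would balance anyway (time of day and fasting). It leaves free one thing that the allocation itself changes: how recently the participant exercised. One arm reaches the 16-week draw at the end of a period of frequent training; the other has no prescribed sessions. The baseline measurement is made before the program starts, so analysing change from baseline does not remove the difference.

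The markers are meant to show how the program works, and the mechanism of interest is an effect of training. If a recent session still moves a marker when blood is drawn, the arm difference at 16 weeks is the sum of two effects that the data cannot take apart. A short-term shift could hide a lower resting level or be read as a training effect.

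The same ambiguity carries into 12 months. Statistical analysis plans a subgroup analysis of continued exercise within the intervention group. Those who continue are also those most likely to have exercised shortly before the 12-month draw.

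**Working it through.** **The plan's own figures.** The article gives no figure on this point. Its sample size is used below only to set the number per arm, and it reproduces. With a two-sided Fisher's exact test, 10% against 40% and alpha 0.05, exact power is 89.8% at 46 per arm and 90.6% at 47. Then 47/(1 − 0.20) = 58.75, rounded up to 59 per arm, or 118. The planned 140 less 20% dropout leaves 70 × 0.8 = 56 per arm.

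**Step 1: exposure at the draw.** Inputs are five sessions a week (Exercise program) and no prescribed sessions in controls (Waitlist control group). Assumptions are one session per day, training days spread at random over the week, and a draw day chosen without regard to them.

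- Share of draws preceded by a training day, full adherence: 5/7 = 71%.
- Share with at least one session in the two preceding days, full adherence: 1 − 1/C(7,2) = 1 − 1/21 = 20/21 = 95%.
- Share preceded by a training day, 50% adherence: 0.5 × 5/7 = 36%.

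**Step 2: what this could do to a marker.** The documents do not say that a single session shifts these markers, or in which direction, by how much or for how long. So let s be an assumed shift, in SD units, still present on the morning after a session, and take exposure in controls as zero. With no true training effect:

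- bias = exposure share × s
- standard error of the arm difference = √(2/56) = 0.189 SD
- chance that a two-sided 5% test rejects = 1 − Φ(1.96 − bias/0.189) + Φ(−1.96 − bias/0.189)

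| Adherence | Assumed s (SD) | Bias (SD) | Rejection rate |
|---|---|---|---|
| 100% | 0 | 0 | 5% |
| 100% | 0.1 | 0.71 × 0.1 = 0.07 | 6.7% |
| 100% | 0.2 | 0.71 × 0.2 = 0.14 | 11.8% |
| 100% | 0.5 | 0.71 × 0.5 = 0.36 | 47.2% |
| 50% | 0.1 | 0.36 × 0.1 = 0.04 | 5.4% |
| 50% | 0.2 | 0.36 × 0.2 = 0.07 | 6.7% |
| 50% | 0.5 | 0.36 × 0.5 = 0.18 | 15.7% |

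The table is a normal approximation for one marker and ignores the small extra variance that mixed exposure would add. Any recent exertion among controls would shrink the bias in proportion to the difference in exposure between the arms.

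**The case against.** **This is a condensed article.** Instructions before a blood draw often sit in a laboratory manual or the full protocol, neither of which is shown. That stands: the article cannot be faulted for lacking a manual. But it does set a sampling rule, down to the centrifuge speed, and it omits the one condition that the trial makes differ by arm. The point is therefore an improvement to a stated rule.

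**The after-effect is not in the documents.** This also stands and limits the point. A reader might infer that the 16-week values do mix acute and training effects, or that the cytokine results will be invalid. The documents support neither. The Discussion says only that exercise can reduce certain inflammatory markers. A fasting morning draw may already put many hours between a session and the sample, although a session on the same morning is not barred.

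**The exposure may be smaller than it looks.** The sessions are advised, the Background stresses poor uptake of exercise, and the example volumes are low (3 to 5 repetitions for 3 sets). Controls are not inactive: eligibility allows up to 150 minutes a week of moderate-to-vigorous activity. So 71% and 95% are upper figures, and at 50% adherence most draws would not follow a training day. The difference between arms becomes smaller but remains.

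**The data for a check are largely collected.** The app logs exercise completion during intervention and follow-up, and ActiGraph measurement is scheduled at the same time points as the cytokines. This is true and makes the fix cheap. But the app log covers only the intervention arm, and the article does not say whether the ActiGraph week comes before the draw.

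**The randomised contrast is still valid.** At 16 weeks and at 12 months it estimates the effect of being offered the program, whatever the timing of the sample. That is right, and calling the 12-month arm comparison confounded would go too far. What is lost is the reading of that contrast as a training mechanism.

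**Conclusion.** The point holds in a limited form. The interval between the last session and the blood draw is neither fixed nor recorded for the draw, and exposure to recent exercise differs by arm by design at 16 weeks: about 71% of intervention draws the morning after a training day at full adherence, about 36% at half adherence. If an after-effect persists to the morning draw, it cannot be told apart from the training effect that the markers are meant to show, and the 12-month comparison of those who continue exercising has the same ambiguity. The size is unknown. It is zero if the effect has cleared. Under assumed shifts of 0.1 to 0.5 SD it is a bias of 0.04 to 0.36 SD across the two adherence levels, and the 47.2% rejection rate is the extreme of that range.

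Two further steps are tempting and have no support in the documents. Nothing in them indicates how long the interval should be, and nothing shows a problem with the order of the blood draw and the functional tests at a visit. The markers are a secondary, mechanistic outcome; the primary outcome and the 118/140 sample size are untouched. This is a cheap improvement.

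**What to change.** Add to Inflammatory biomarkers that every draw, in both arms and at all three time points, follows one common minimum interval without a PF-Life session or unaccustomed exertion. The investigators should set its length. The prescribed training need not change: five sessions on separate days leave two days a week without one, and the appointment can be booked after the participant's own rest days.

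Record at each draw the date and time of the last exertion. In the intervention arm it can be checked against the app log, and in both arms against ActiGraph data where the wear period covers the days before the draw.

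Add a sensitivity analysis of the cytokines that uses this interval, for example by repeating the arm comparison among draws that met the minimum. Time since exertion is a post-randomisation variable linked to allocation, so this analysis can support the scheduling rule but not replace it.

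The cost is a short protocol addition, one extra data item per draw and slightly tighter appointment windows. The rule is best set before the 16-week draws begin, since an interval not recorded then may be hard to recover, above all in controls.

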### Outcome measures

Table 1 provides a detailed summary of primary and secondary outcome measures for each assessment time point. Data collectors will be blinded to group assignments.

**Table 1 tab1:** Overview of primary and secondary outcomes, outcome measures, and assessment time points.

Outcomes	Outcome measures	Screening	Baseline	16 weeks	1-years
Eligibility assessment	Inclusion criteria	√			
	Exclusion criteria	√			
Primary outcomes					
Pre-frailty assessment	Fried frailty phenotype	√	√	√	√
Secondary outcomes					
Body composition	Body mass index, body fat mass, body fat percentage, fat-free body mass, fat-free mass percentage, and visceral fat level	√	√	√	√
Bone mineral density	Bone mineral density	√	√	√	√
Functional performance assessment	30-s chair rise test	√	√	√	√
	30-s arm curl test	√	√	√	√
	Hand grip strength	√	√	√	√
	Chair sit and reach test	√	√	√	√
	Back scratch test		√	√	√
	Timed up and go test		√	√	√
	Single-leg stance test		√	√	√
	4-m gait speed test		√	√	√
	2-min step test		√	√	√
Physical activity level assessment	Sedentary time (min/d), energy expenditure (MET/h), LPA (min/d), MVPA (min/d)		√	√	√
Inflammatory cytokines	Chemokines (CXCL8/IL-8, CCL5/RANTES, CXCL9/MIG, CCL2/MCP-1, CCL11/Eotaxin and CXCL10/IP-10, CCL4/MIP-1β, CCL7/MCP-3, CXCL1/GROα, CCL3/MIP-1α, CCL28/CTACK, and CXCL11/SDF-α)		√	√	√
	Cytokines (IL-2, IL-3, IL-4, IL-5, IL-6, IL-7, IL-9, IL-10, IL-12, IL-13, IL-15, IL-16, IL-17A, IL-18, IL-1β, TNF-a, TNF-β, IFNγ, and IFNα)		√	√	√
Exploitative outcome assessment	Medical and demographical data	√	√	√	√
	Sustainability		√	√	√

√, data will be obtained; MET, metabolic equivalents of task; LPA, low physical activity; MVPA, moderate-to-vigorous physical activity.

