### Statistical analysis

All data will be processed and analyzed using IBM SPSS 22.0 statistical analysis software, and a significance level of 5% will be used. Independent *t*-tests or *Mann–Whitney* tests will be used to compare demographic and other baseline characteristics of participants pre-intervention. A two-way ANOVA test with repeated measures for each of the variables will be applied to assess the effect of the program at pre-intervention, post-intervention, and follow-up stages on complexity (non-linear measures) vs. traditional (linear) measures of the proportion of pre-frailty, BC vs. BMD, PA vs. sedentary behaviors, FF (4-m gait speed test, TUG test, chair sit and reach test, back scratch test, single leg stance test, HGS, and 30-s chair rise test), and inflammatory cytokines. A subgroup analysis of the intervention group will be conducted after 12-month follow-up to explore the potential impact of continued exercise on the sustainability of the intervention effects. Multiple equation chain interpolation (MICE) is used to handle missing data, and where missing data are associated with observed covariates, propensity scores may be used to weight observations or adjust models to balance groups defined by missing data status. Statistical analyses will be performed using per-protocol and intent-to-treat (ITT) analyses in the case of potential dropouts.

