To explore the underlying mechanisms, the effects of lifestyle-integrated multicomponent exercise on BC and FF in pre-frail older adults will be assessed. Multicomponent exercise has been found to reduce body fat loss, increase fat-free mass, and improve physical function in both healthy and frail older adults, suggesting that BC and physical dysfunction may serve as potential markers and modifiable risk factors for frailty (63, 64) and therefore may be a key target for treating pre-frail older adults. In addition, chronic low-grade inflammation is recognized as a key factor contributing to frailty and is a hallmark of aging. It has been found that higher levels of inflammatory mediators in older populations can directly influence the onset of frailty by degrading proteins or indirectly influencing metabolic pathways, leading to frailty (6). Levels of pro-inflammatory chemokines and cytokines such as interleukin-1β (IL-1β), interleukin-6 (IL-6) and tumor necrosis factor-α (TNF-α) are known to be elevated in frail individuals, whereas levels of the anti-inflammatory cytokines interleukin-4 (IL-4) or interleukin-10 (IL-10) are reduced (65). However, there is a lack of evidence on the beneficial effects of exercise interventions based on digital technology on inflammatory levels in pre-frail older adults, particularly in terms of inflammatory biomarkers. However, physical exercise can reduce certain inflammatory biomarkers in aging older adults. Since the balance between inflammatory and anti-inflammatory biomarkers is thought to be a determinant of the severity of aging-related diseases, understanding the effects of PA on the inflammatory profile of frail and aging older adults will provide insights into the mechanisms by which exercise provides benefits and guide future customization of exercise programs for frail older adults.

To the best of our knowledge, this is the first RCT to evaluate the effectiveness of a novel and innovative digital lifestyle-integrated multicomponent exercise program in reversing pre-frailty in community-dwelling older adults and shed light on the underlying inflammatory mechanisms from a scientific perspective. The trial will use rigorous methods to reduce biases, such as randomization, active recruitment strategy, rigorous eligibility screening, innovative design of mHealth technology based on behavioral change theory, blinding of outcome assessors and data analysts, and statistical analyses based on ITT principles.

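### Each inflammatory marker is tested at 5% with no error control stated, and it is unclear whether the tested set is the 31 named markers or all 48 assayed

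*Protocol article*

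**What the plan says.** - **Panel size.** The Inflammatory biomarkers section announces "Simultaneous measurement of 48 different inflammatory markers in plasma samples by Luminex assay". It then says that these include the chemokines "CXCL8/IL-8, CCL5/RANTES, CXCL9/MIG, CCL2/MCP-1, CCL11/Eotaxin and CXCL10/IP-10, CCL4/MIP-1β, CCL7/MCP-3, CXCL1/GROα, CCL3/MIP-1α, CCL28/CTACK, and CXCL11/SDF-α" and the cytokines "IL-2, IL-3, IL-4, IL-5, IL-6, IL-7, IL-9, IL-10, IL-12, IL-13, IL-15, IL-16, IL-17A, IL-18, IL-1β, TNF-a, TNF-β, IFNγ, and IFNα".
- **Outcome definition.** Table 1, under Outcome measures, lists the same markers as the outcome. It does not mention 48 and does not present the list as partial.
- **Status.** The Secondary outcomes section reads "Secondary outcomes are the change in BC, FF, bone mineral density (BMD), inflammatory cytokines, PA, and sedentary behaviors". The hypothesis at the end of the Background also covers a change in inflammatory cytokines, without naming a marker or a direction.
- **Analysis.** The Statistical analysis section says "a significance level of 5% will be used" and "A two-way ANOVA test with repeated measures for each of the variables will be applied"; inflammatory cytokines are in the list of variables. The article gives no adjustment, hierarchy, lead marker or composite score for the panel.
- **Intended use.** The Abstract is mixed. Its Methods paragraph says the markers serve to explore mechanisms, and its Discussion paragraph says they will elucidate them.

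**The concern.** The rule as written is one 5% test per marker over a long panel, and the hypothesis is loose enough that any marker moving in either direction could be taken as support. A panel tested in this way is expected to give one or two significant markers even if the program affects none of them. The results could not then separate a real inflammatory response from chance.

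The unclear set adds to this. If 48 markers are assayed and 31 are the listed outcome, a reader of the results cannot tell how many tests lie behind the significant ones. At stake are the mechanism claims, which are a stated aim of the trial; the primary comparison does not depend on them.

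**Working it through.** **Inputs**
- Level per test: 0.05 (Statistical analysis).
- Markers assayed: 48 (Inflammatory biomarkers).
- Markers named: 12 chemokines and 19 cytokines, counted from the lists in Inflammatory biomarkers and in Table 1.
- Correlation between markers: not given, so a range from 0 to 0.9 is assumed.

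**Step 1: the plan's own figures.** Named markers: 12 + 19 = 31. Unnamed: 48 − 31 = 17. The article states no error rate for the panel. Its one derived design figure, 118 participants, reproduces: an exact two-sided Fisher test of 10% against 40% first reaches 90% power at 47 per group (power 0.906), and 47 / (1 − 0.20) = 58.75, rounded up to 59 per group, or 118. That figure concerns the primary outcome only.

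**Step 2: expected false positives with no true effect.** Expected number = m × 0.05.
- 31 markers: 31 × 0.05 = 1.55.
- 48 markers: 48 × 0.05 = 2.40.

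Expectations add whatever the dependence, so correlation does not change these values.

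**Step 3: chance of at least one, under independence.** Chance = 1 − 0.95^m.
- 31 markers: 1 − 0.95^31 = 0.796.
- 48 markers: 1 − 0.95^48 = 0.915.

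**Step 4: chance of at least one, with correlated markers.** Test statistics were simulated as normal with one common correlation ρ (100,000 runs), counting absolute values above 1.96.

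| Assumed ρ | 31 markers | 48 markers |
|---|---|---|
| 0 (exact) | 79.6% | 91.5% |
| 0.3 | 67% | 80% |
| 0.5 | 51% | 61% |
| 0.7 | 34% | 40% |
| 0.9 | 17% | 19% |

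The simulated mean number of false positives stayed at 1.53 to 1.57 (31 markers) and 2.38 to 2.40 (48 markers) throughout, in line with Step 2.

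**Step 5: what Benjamini-Hochberg would ask.** The k-th smallest of m p-values is compared with k × 0.05 / m. The strictest threshold (k = 1) is 0.05 / 31 = 0.0016 or 0.05 / 48 = 0.0010. It relaxes as more markers show an effect.

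**The case against.** The strongest reply is that this is a condensed article, that its analysis plan is not shown, and that multiplicity rules for a secondary panel are often placed there. This stands in part: the article cannot be read as ruling out error control, only as stating none. But it is not merely silent. It fixes a 5% level and an analysis for each variable, and that rule, followed as written, gives the figures above.

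A second reply is that the panel is exploratory. The Abstract does use that word once. Table 1, however, has a separate bottom tier for such items (printed as 'exploitative'), and the markers sit above it among the secondary outcomes.

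A reader might also infer several stronger things that the documents do not support:
- **That 48 against 31 is a miscount.** The text says the 48 include the listed markers, so the list may be partial. What is shown is an undefined outcome set.
- **That all 48 will be tested.** No section says the 17 unnamed markers will be tested or selectively reported. The 31 in Table 1 are the supported case and 48 is an upper bound.
- **That the counts double, to 3.1 and 4.8, because there are two follow-up assessments.** The plan applies one repeated-measures ANOVA per variable across all time points, not a separate test at each visit.
- **That 80% or 91% is the chance of a false finding.** Those values need independence and no true effect on any marker. Markers from one assay are plausibly correlated, which lowers the chance considerably.
- **That the mechanism conclusion will probably be false.** That depends on how many markers are truly affected, which is unknown. The Discussion itself says that exercise can reduce certain inflammatory markers.

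**Conclusion.** The point holds in limited form. The written rule tests each inflammatory marker at 5% with no error control stated, and the article leaves open whether 31 or 48 markers are tested. With no true effect and one test per marker, 1.55 false positives are expected over 31 markers and 2.4 over 48; this does not depend on correlation. The chance of at least one does. It runs from 80% (31) or 91% (48) under independence down to about 17% or 19% at an assumed common correlation of 0.9, which is still more than three times the nominal 5%.

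The consequence is that chance and real marker effects could not be told apart, so unadjusted results would be weak evidence of mechanism. The primary outcome and the sample size are unaffected.

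**What to change.** 1. State whether the 31 named markers or all 48 form the outcome. If 48, name the other 17. Make the text and Table 1 agree, and report every marker assayed.
2. Test one group-by-time effect per marker, and apply Benjamini-Hochberg control at a 5% false discovery rate over the full stated set.
3. Describe markers significant only at unadjusted 5% as exploratory, not as evidence of mechanism.

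A short lead set with Holm correction is an option, not a requirement. The Discussion offers candidates: it says that "interleukin-1β (IL-1β), interleukin-6 (IL-6) and tumor necrosis factor-α (TNF-α) are known to be elevated in frail individuals" and that IL-4 and IL-10 are reduced. It gives these as background on frailty and does not propose them as lead markers for this pre-frail population.

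The cost is about one paragraph and no new data. Individual markers need stronger evidence to be called significant: the smallest p-value must reach at least 0.0016 (31 markers) or 0.0010 (48) if it is the only one to pass.
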